## Abstract

**Background:**

One single-center randomized clinical trial showed that INTELLiVENT-adaptive support ventilation (ASV) is superior to conventional ventilation with respect to the quality of ventilation in post-cardiac surgery patients. Other studies showed that this automated ventilation mode reduces the number of manual interventions at the ventilator in various types of critically ill patients. In this multicenter study in patients post-cardiac surgery, we test the hypothesis that INTELLiVENT-ASV is superior to conventional ventilation with respect to the quality of ventilation.

**Methods:**

“POStoperative INTELLiVENT-adaptive support VEntilation in cardiac surgery patients II (POSITiVE II)” is an international, multicenter, two-group randomized clinical superiority trial. In total, 328 cardiac surgery patients will be randomized. Investigators screen patients aged > 18 years of age, scheduled for elective cardiac surgery, and expected to receive postoperative ventilation in the ICU for longer than 2 h. Patients either receive automated ventilation by means of INTELLiVENT-ASV or ventilation that is not automated by means of a conventional ventilation mode. The primary endpoint is quality of ventilation, defined as the proportion of postoperative ventilation time characterized by exposure to predefined optimal, acceptable, and critical (injurious) ventilatory parameters in the first two postoperative hours. One major secondary endpoint is ICU team staff workload, captured by the ventilator software collecting manual settings on alarms. Patient-centered endpoints include duration of postoperative ventilation and length of stay in ICU.

**Discussion:**

POSITiVE II is the first international, multicenter, randomized clinical trial designed to confirm that POStoperative INTELLiVENT-ASV is superior to non-automated conventional ventilation and secondary to determine if this closed-loop ventilation mode reduces ICU team staff workload. The results of POSITiVE II will support intensive care teams in their choices regarding the use of automated ventilation in postoperative care of uncomplicated cardiac surgery patients.

**Trial registration:**

Clinicaltrials.gov NCT06178510. Registered on December 4, 2023.

**Supplementary Information:**

The online version contains supplementary material available at 10.1186/s13063-024-08296-2.

## Background

Postoperative ventilation, often needed following cardiac surgery, may injure the lungs [1]. Lung-protective ventilation consists of ventilation using a properly-sized tidal volume (*V*_T_) to prevent volutrauma and barotrauma [2, 3], low pressures and energy to avoid energy trauma [4–7], and low levels of oxygen in inspired air (FiO_2_) to minimize the risk of chemotrauma [8, 9]. Applying lung-protective ventilation is challenging and time-consuming because it requires complex titrations of ventilator settings according to a patient’s continuously changing individual needs [10], which is particularly true for post-cardiac surgery patients scheduled for fast-track weaning from mechanical ventilation.

Automated ventilation is increasingly attractive for clinical use [11] as it improves the quality of ventilation and potentially offers support to diminished ICU team staff [12–14]. With automated ventilation, ventilator settings that are typically under control of the ICU team staff are under control of algorithms that form the basis of the automated ventilation mode. INTELLiVENT-ASV, one sophisticated automated ventilation mode, targets ventilation and oxygenation goals based on lung mechanics, whereby it automatically adjusts, breath-by-breath, *V*_T_, respiratory rate (RR), positive end-expiratory pressure (PEEP), and FiO_2_ [15]. Several studies have shown INTELLiVENT-ASV to be safe and effective with regard to lung-protective ventilation [16] and one single-center randomized clinical trial named “POStoperative INTELLiVENT-adaptive support VEntilation in cardiac surgery patients” (POSITiVE), showed INTELLiVENT-ASV to be superior to non-automated ventilation with respect to quality of ventilation in patients receiving postoperative ventilation after cardiac surgery [17].

Several studies showed that INTELLiVENT-ASV reduces the number of manual interventions by intensive care unit (ICU) team staff in various types of patients [12–14]. It cannot yet be concluded though if INTELLiVENT-ASV reduces ICU team staff workload since workload may also involve other aspects of care, such as but not limited to presetting the ventilator for use of automated ventilation, the number of blood gas analysis needed, the time spend with monitoring ventilatory support, and the number of and responses to alarms.

The here proposed randomized clinical trial, the successor of the abovementioned single-center POSITiVE study, will test the hypotheses that automated ventilation by means of INTELLiVENT-ASV is superior to non-automated ventilation by means of conventional ventilation with respect to quality of ventilation in postoperative ventilation in patients after cardiac surgery. We further hypothesize that INTELLiVENT-ASV reduces the ICU team staff workload and is non-inferior to, i.e., as good as non-automated ventilation with respect to duration of ventilation and length of stay in ICU.

## Methods

### Objectives and design

The “POStoperative INTELLiVENT-adaptive support VEntilation in cardiac surgery patients II” (POSITiVE II) study is an investigator-initiated, international, multicenter, parallel, randomized clinical trial that compares automated ventilation by means of INTELLiVENT-ASV with ventilation that is not automated by means of conventional ventilation in patients planned for elective cardiac surgery and expected to need postoperative ventilation in an intensive care unit for at least 2 h.

The primary objective is to compare the two ventilation strategies with respect to quality of ventilation. One major secondary objective is to compare the two ventilation strategies with respect to ICU team staff workload, including manual ventilator settings and alarms; we will also compare the two ventilation strategies with respect to patient-centered endpoints like duration of ventilation, and length of stay in ICU.

The study will be conducted according to the Good Clinical Practice guidelines and comply with the principles of the Declaration of Helsinki, national and international regulatory requirements, and general data protection regulations. The study is registered in a public registry, and a finalized statistical analysis plan will be prepublished before cleaning and closing of the database.

### Study population

POSITiVE II will include patients planned for elective cardiac surgery and to receive postoperative ventilation in an ICU.

In order to be eligible to participate in this study, a patient must meet the following criteria: aged above 18 years of age, scheduled for elective cardiac surgery, and expected to receive postoperative ventilation in the ICU for longer than 2 h. Before surgery, a potential patient who meets any of the following criteria will be excluded from participation in this study if: (i.) the surgical procedure concerned an emergency or semi-elective intervention (precluding informed written consent) or (ii.) any surgery other than coronary artery bypass grafting (CABG), valve replacement or repair, or a combination of these (i.e., patients planned for surgery for congenital heart disease, or scheduled for heart transplantation, will be excluded). Patients are also excluded if: (iii.) enrolled in another interventional trail; (iv.) no written informed consent is obtained; (v.) in case of a history of recent pneumectomy or lobectomy; or (vi.) COPD with oxygen at home; (vii.) has a body mass index higher than 35; or (viii.) a preoperative forced expiratory volume in the first second (FeV1)/forced vital capacity (VC) of less than 50% (if available); or (ix.) a preoperative arterial oxygen partial pressure (PaO2) < 60 mm Hg (at room air); or (x.) preoperative arterial carbon dioxide partial pressure (PaCO2) of more than 50 mm Hg; or (xi.) preoperative left ventricular ejection fraction of less than 30% (if available); or (xii.) preoperative systolic pulmonary artery pressure higher than 60 mm Hg (if available); or (xiii.) preoperative left ventricular mechanical support, e.g., Impella®; or (xiv.) preoperative use of veno-venous or veno-arterial extracorporeal support (ECMO). At the end of surgery, patients are additionally excluded if: (xv.) weaning from intraoperative extracorporeal support is not possible due to surgical complications or (xvi.) a cardiac assist device is implanted.

### Standard ventilation management

In the ICU, subjects are cared for by dedicated board-certified ICU team. Changes in treatment are implemented based on observations by ICU team and physicians and according to the recommendations in the local guideline for postoperative care. Automated ventilation is generally initiated within 10 min after ICU arrival, with automated adjustments of minute volume, PEEP, and FiO_2_ activated. Extubation is performed according to criteria described in the local protocol.

After arrival in the ICU, the attending caregiver initiates the ventilator mode of choice, using lung-protective ventilator settings, guided by blood gas analyses. Use of another automated mode is *not* allowed: only standard pressure-controlled ventilation or volume-controlled ventilation modes are allowed in passive patients and assisted breathing in active patients. *V*_T_ and RR, and PEEP and FiO_2_ are set and adjusted to keep etCO_2_ and PaCO_2_ in range. Typically, PEEP is limited to 5 to 12 cm H_2_O, FiO_2_ is limited to 30 to 100%. In case of a difference between PaCO_2_ and etCO_2_ of ≥ 5 mm Hg, the etCO_2_ target is adjusted. As soon as a patient displays spontaneous breathing efforts, the ventilator is switched from controlled to supported ventilation. The patient is extubated according to the local protocol; quantitative neuromuscular monitoring (e.g., train-of-four (TOF) monitoring) should be considered in case multiple doses of muscle relaxants are given in the operating room, or in the ICU––in those cases, before extubation residual curarization should be addressed (e.g., TOF > 0.9).

### Intervention

The intervention tested is named “INTELLiVENT-ASV”, an automated ventilation mode available at Hamilton Medical AG ventilators (Hamilton Medical AG, Bonaduz, Switzerland) and intended to be used in patients that need ventilation in an ICU. INTELLiVENT-ASV is a fully automated mode of ventilation, targeting the lowest work and force of breathing, through breath-by-breath adaptation of *V*_T_ and RR, and PEEP and FiO_2_ based on patient activity, airway pressures and continuous pulse oximetry readings and end-tidal carbon dioxide monitoring. It also uses a weaning protocol and spontaneous breathing trials to facilitate weaning.

After arrival in the ICU, subjects start as soon as possible with INTELLiVENT-ASV. The attending caregiver initiates this automated ventilation mode, typically within 10 min after arrival in the ICU, when the results of the first blood gas analyses become available. Automatic adjustments for percentage of alveolar minute volume, PEEP, and FiO_2_ are activated and standard thresholds are set: PEEP is limited to 5 to 12 cm H_2_O, FiO_2_ is limited to 30 to 100%, and a “normal lung condition” is chosen. In case of a difference between PaCO_2_ and etCO_2_ of ≥ 5 mm Hg, the etCO_2_ target is shifted as described in the clinical guideline in use in the participating ICU. If clinically indicated, the target range for SpO_2_ can be manually adjusted. The options “Quick Wean” and “automated spontaneous breathing trials” are activated at start of ventilation by means of INTELLiVENT-ASV.

With INTELLiVENT-ASV, manually switching off one or more of the automated controllers by the attending caregiver (i.e., due to poor sensor signal quality) is allowed at any point during the study, in compliance with standard ventilation management of the participating ICU. According to a standard operating protocol, in case of a large discrepancy between SpO_2_ and SaO_2_ (SaO_2_ > 5% lower than SpO_2_), the automated FiO_2_ and PEEP controllers should be switched off, and in case of a minute ventilation of > 200% of the predicted minute volume, the minute volume controller should be switched off.

### Standard procedures beyond ventilator management

Routine general anesthesia is performed according to the specific expertise and routine clinical use of each participating center. General anesthesia achieved by using both volatile anesthetics and intravenous anesthetics are both allowed.

Postoperative pain management, sedation, physiotherapeutic procedures, and fluid management will be performed in the intra-operative and/or post-operative period according to the specific expertise and routine clinical use of each center. There are no restrictions regarding concomitant care during the trial. The investigators suggest to adhere to the enhanced recovery after surgery (ERAS) guidelines (http://erassociety.org/guidelines/list-of-guidelines/): (1) to perform postoperative pain management in order to achieve a VAS pain score below 4 and regional or neuraxial analgesia can be used whenever indicated; (2) to use physiotherapy by early mobilization, deep breathing exercises with and without incentive spirometry, and stimulation of cough in the postoperative period; (3) to avoid fluid overload (according to the discretion of the attending anesthesiologist in the operating room and in the ICU); and (4) to use appropriate prophylactic antibiotics according to institutional standards. Furthermore, regarding surgical perioperative procedures, the investigators suggest adhering to the Safe Surgery Checklist from the World Health Organization (Safe surgery [www.who.int]).

### Minimization of bias

In order to prevent dropouts, randomization is performed shortly before the start of surgery as soon as it is certain the surgery will proceed and there is the availability of a ventilator that can be used for the study. Randomization will then be performed by local investigators using the Castor platform [www.castoredc.com]. Included patients will be randomly allocated in a 1:1 ratio to the INTELLiVENT group or to non-automated ventilation group. The allocation sequence will be computer-generated, using the Castor randomization module with permuted blocks of different block sizes, with a maximum block size of 8 and stratified per center.

Further minimization of bias will be achieved by involving at least two independent investigators per site. Investigator responsible for the preoperative and postoperative care cannot be kept blind due to the nature of the intervention tested. All analyses are preplanned, i.e., before closing of the database, and will be performed by an investigator that remains blinded for treatment allocation.

### Study endpoints

The primary outcome is quality of ventilation, which is the proportion of *time* spent in three predefined and previously used zones of ventilation (Appendix 1) in the first 2 h of postoperative ventilation, as used before in previous studies of automated ventilation [17, 18].

Zones of ventilation used to define the primary outcome: for tidal volume (VT ml/kg PBW), critical denotes over 12, acceptable spans 8 to 12, and optimal falls at or below 8; regarding maximum inspiratory pressure (Pmax, cm H2O), critical signifies 36 or higher, acceptable encompasses 31 to 36, and optimal is 30 or less. End-tidal CO2 (etCO2, mmHg) falls into critical if below 25 or at 51 and above, acceptable between 25 and 30 or 46 and 51 and optimal between 30 and 46. Finally, oxygen saturation (SpO2, %) is critical under 85, acceptable if over 98 or between 85 and 93, and optimal between 93 and 98, or over 93 with FiO2 ≤ 40%.

As an add to the primary endpoint, next to *time* spent in predefined zones, we will also calculate *proportion* of breath in predefined zones as secondary endpoint. Also, we will measure ICU team staff workload, which is captured by the ventilator software collecting data on alarms (number of alarms, types of alarm, duration of alarm, responses to alarm, alarm settings and adjustments, breath-by-breath alarm data, and any manual intervention at the ventilator) during postoperative care in the ICU (Appendix 2), as used before in previous studies [12–14, 19].

Other secondary endpoints are duration of postoperative ventilation and ICU length of stay. In addition, we will collect and compare patient–ventilator asynchrony requiring deepening of sedation and/or administration of muscle relaxants; hospital length of stay; and mortality in ICU and hospital.

### Study visits and data collection

Patients scheduled for cardiac surgery in participating centers will be screened for eligibility by anesthesia staff or research personnel to whom this task has been delegated. Patient characteristics of screened patients meeting the inclusion criteria will be recorded, including age category of the subject, date of screening, and reason for not enrolling (Fig. 1).

**Fig. 1 Fig1:**
[figure not shown]
Schedule of enrolment, interventions, and assessments. **a** breath-by-breath analysis of ventilation parameters and variables in a time frame of 2 hours early after start of invasive ventilation; **b** for a maximum of 24 hours or until extubation; **c** for a maximum of 6 hours or until extubation

Patients will be assessed before and during surgery, on postoperative days in the ICU, and the day before hospital discharge. Clinical data, ventilation data, and of outcomes will be captured within this timeframe.

Preoperative variables will be collected at pre-anesthetic visit or before induction of general anesthesia. The following variables are recorded—sex; age; height; weight; functional status; physical status (according to the American Society of Anesthesiologists score); frailty score (if available); cardiac status (heart failure, according to the New York Heart Association score, acute coronary syndrome, or persistent ventricular tachyarrhythmia’s); chronic obstructive pulmonary disease (if inhalation therapy and/or systemic steroids are used); respiratory infection in the last month; smoking status; type of cardiac surgery (CABG, valve reconstruction, valve replacement, combined CABG and valve surgery) and the surgical approach (sternotomy, hemi-sternotomy, thoracotomy, or minimal invasive procedure); and vital parameters (tympanic temperature, respiratory rate, oxygen saturation (SpO_2_), blood pressure, heart rate).

The patients will be assessed daily until the day after successful extubation, as well as on the last day before ICU and hospital discharge. In cases of re-intubation, timing of and reasons for re-intubation will be recorded. One investigator, blinded to the randomized intervention, will collect postoperative variables. The following variables are recorded on the first 5 days after surgery and the day before discharge: patient status (location, i.e., in hospital or at home—alive or deceased, and in the case of the latter the day of dying); occurrence of postoperative pulmonary complications; occurrence of extra pulmonary complications; requirement and duration of postoperative mechanical ventilation; re-admission to the intensive care unit (ICU) within the current hospitalization after initial ICU discharge; unplanned admission to another monitored ward; physiotherapy (e.g., for early mobilization, deep breathing exercise or stimulation of cough); urine output; need of renal replacement therapy; vital parameters including heart rate, tympanic temperature, oxygen saturation, respiratory rate, visual analogue scale pain score and blood pressure; impairment of wound healing and surgical wound infection; and blood tests including glucose, urea, creatinine, hemoglobin, C-reactive protein, and white blood cell count.

High-granular ventilation data will be captured using data storage devices or a dedicated laptop connected directly to the communication port at the ventilator:Breath-by-breath ventilation data is captured—data collection continues until tracheal extubation; data are stored for further analysis as described before [17, 18]; andManual ventilator settings and alarms, breath-by-breath alarm data, and any manual intervention at the ventilator is captured—this is done in the same way as described for the breath-by-breath ventilation data.

### Informed consent

All eligible patients will be informed about the study and asked for written informed consent before surgery. This will be done at the preoperative screening outpatient clinic, by telephone call or at admission the day before surgery. All approached patients will have sufficient time (at least 12 h) for consideration before the informed consent form is signed. No study-related actions will be performed before written informed consent is obtained. Informed consent will be documented on a paper form and signed by the patient and attending researcher. One signed informed consent form remains with the patient, the other will be stored in a designated secure folder in the respective participating center.

### Study dropouts and missing data

Subjects can leave the study at any time for any reason if they wish to do so without any consequences. The investigator can decide to withdraw a subject from the study for urgent medical reasons.

Subject will be classified as drop outs for the analyses of the endpoint “quality of ventilation” and “ICU team staff workload” if they did not receive postoperative ventilation for at least 2 h. This also means that if a patient is extubated in the operating room, that patient is considered a dropout. At no time a patient will remain intubated to reach at least 2 h of postoperative ventilation, i.e., extubation is never delayed for study purposes. A dropout rate of 5% has been accounted for in the sample size.

In case of withdrawal after randomization, the subject will not be replaced. Captured data until the moment of withdrawal will be stored and used for analysis. If the subject has not been randomized yet, the subject will be replaced to reach the intended sample size of patients.

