### Statistical analysis

A full statistical analysis plan will be published online before the end of recruitment. All statistical analyses will be conducted according to the modified intention-to-treat principle considering all patients in the treatment groups to which they were randomly assigned, excluding cases lost to follow-up due to withdrawal of consent or cancelation of surgery. For both arms, the baseline characteristics will be expressed as counts and percentages, means and standard deviations, or medians and interquartile ranges, depending on normality of data distribution.

Data analysis will be performed blinded for the allocated study intervention. In all analyses, statistical uncertainties will be quantified with two-sided 95% confidence intervals. A two-sided *p*-value < 0.05 will be considered statistically significant. We will not adjust the *p*-value for multiple comparisons.

For the noninferioirty assessment of duration of ventilation, a one-sided noninferiority hypothesis test with a significance level of 0.025 and presented with a one-sided 97.5% confidence interval will be used. If noninferiority is confirmed, superiority will be tested considering a two-sided 95% confidence interval. Since the proposed approach will use a hierarchical closed-testing procedure examining a single confidence interval, no adjustment of the overall type I error will be done.

Statistical analysis will be performed using the free software program “R” (R Core Team, 2020, Vienna, Austria).

The effects of the intervention on quality of ventilation are analyzed and reported as done in previous studies of automated ventilation, i.e., the *time* spent in predefined zones of ventilation [17, 18]. As an add to the primary endpoint, next to *time* spent in predefined zones, we will also calculate *numbers* of breath in predefined zones. For details, see Appendix 1.

The impact of the intervention on ICU team staff workload is reported as in previous studies collecting data on alarms [12–14, 19].

All other endpoints, including duration of ventilation and ICU and hospital length of stay are reported as numbers and proportions.

Patient flows will be presented in a consolidated standard of reporting trials (CONSORT) flowchart.

Patients’ baseline characteristics will be presented per study arm. The proportion of patients who were treated according to their treatment assignment will be reported by treatment group.

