Comparisons of the collected variables will be performed using *χ*^2^ tests for equal proportion, Student’s *t*-test for normally distributed data and Wilcoxon rank sum tests otherwise.

The database will be locked as soon as all data are entered and all discrepant or missing data are resolved—or if all efforts are employed and we consider that the remaining issues cannot be fixed. At this step, the data will be reviewed before database locking. After that, the study database will be locked and exported for statistical analysis. At this stage, permission for access to the database will be removed for all investigators, and the database will be archived.

No or minimally losses to follow-up for the primary and secondary outcomes are anticipated. Complete case analysis will be carried out for all the outcomes, that is, excluding patients with missing data in the outcome of interest. However, if any missing data is found for the primary outcome, a sensitivity analysis using multiple imputations and estimating equation methods will be performed.

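### Medical withdrawal from the study, combined with complete-case analysis, can truncate or lose ventilation duration, stay and mortality for patients who deteriorate, in conflict with the plan's own analysis set

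*Protocol article*

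**What the plan says.** All references are to the protocol article.

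- **Study dropouts and missing data.** "The investigator can decide to withdraw a subject from the study for urgent medical reasons". What is left is the study, not the assigned ventilation mode, and urgent medical reasons are not defined further. The section adds "In case of withdrawal after randomization, the subject will not be replaced" and "Captured data until the moment of withdrawal will be stored and used for analysis".
- **Minimization of bias.** "Investigator responsible for the preoperative and postoperative care cannot be kept blind due to the nature of the intervention tested".
- **Statistical analysis, analysis set.** Patients are analysed in their randomised group under a modified intention-to-treat principle, "excluding cases lost to follow-up due to withdrawal of consent or cancelation of surgery". Withdrawal by an investigator is not on that list. The Discussion describes the analysis as intention-to-treat.
- **Statistical analysis, missing data.** "Complete case analysis will be carried out for all the outcomes, that is, excluding patients with missing data in the outcome of interest". The only further provision is that "if any missing data is found for the primary outcome, a sensitivity analysis using multiple imputations and estimating equation methods will be performed".
- **Intervention.** The plan allows "manually switching off one or more of the automated controllers by the attending caregiver" at any point during the study, so departing from full automation does not in itself require leaving the trial.
- **Study endpoints.** Duration of ventilation, ICU and hospital length of stay, and ICU and hospital mortality are secondary endpoints.

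**The concern.** The withdrawal rule does not separate stopping the assigned mode from leaving the study. Its trigger is medical urgency, so the patients it affects are likely to differ in prognosis from those who stay. It can be invoked by someone who knows the allocation. Loss of outcome data under this rule would be informative and could differ between arms.

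The most exposed endpoint is duration of postoperative ventilation. It sets the sample size (328 rather than the 220 needed for quality of ventilation) and is tested for non-inferiority with a margin of ¾ h. Losing long-ventilated patients from the INTELLiVENT-ASV arm would make that arm look shorter and favour a false claim of non-inferiority. Losing them from the conventional arm would act the other way. ICU and hospital stay are exposed in the same manner, and a death after withdrawal may not be counted as an endpoint.

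**Working it through.** **1. Following the rules for one patient.** Suppose a patient is withdrawn for urgent medical reasons while still ventilated.

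- The analysis-set rule keeps the patient in, because neither consent withdrawal nor cancelled surgery applies.
- The withdrawal rule provides for data up to that moment. No section provides specifically for collection afterwards.
- If the captured data are used as they stand, ventilation duration is cut at withdrawal. If the outcome is treated as missing, the complete-case rule drops the patient. Both readings remove hours from the long end of the distribution.
- No sensitivity analysis is planned for this outcome, since multiple imputation is reserved for the primary outcome.

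So the analysis-set definition retains the patient, while the withdrawal and complete-case rules together can take the outcome away.

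**2. The plan's own figure.** Inputs from Sample size calculation: SD 5.0 h, margin 0.75 h, one-sided alpha 0.025, power 90%, 1:1 allocation. The formula is n per arm = 2 × SD² × (1.96 + 1.2816)² / (margin + assumed benefit)².

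- Benefit 1.05 h (70% of 1.5 h): 2 × 25 × 10.51 / 1.80² = 162.2, so 163 per arm by the normal approximation and 164 by the noncentral t. The stated 164 reproduces.
- Benefit 1.01 h as printed: 2 × 25 × 10.51 / 1.76² = 169.6, so 170 per arm; power at 164 is 89.0%.

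The point here does not depend on which benefit was used. It needs only the margin, the SD and the arm size.

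**3. Possible size of the shift.** The document gives neither the number of medical withdrawals nor how long those patients would have been ventilated, so both are assumptions. (The 5% dropout allowance concerns patients ventilated for less than 2 h and does not supply the number.) If k of 164 patients are lost from one arm and their mean duration exceeds that of the others by D hours, the arm's mean falls by k × D / 164. If durations are truncated instead of dropped, the same formula holds with D as the mean hours left uncounted.

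The standard error of the difference is 5.0 × √(2/164) = 0.552 h. If the true difference lies exactly at the margin and the loss is in the INTELLiVENT-ASV arm, the one-sided type I error is Φ(shift/0.552 − 1.96).

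| Assumed loss, one arm only | Shift (h) | Share of 0.75 h margin | Type I error at the margin |
|---|---|---|---|
| None, or equal loss of similar patients in both arms | about 0 | about 0% | 2.5% |
| 2 patients, 12 h excess | 2 × 12/164 = 0.15 | 20% | 4.6% |
| 3 patients, 24 h excess | 3 × 24/164 = 0.44 | 59% | 12% |
| 5 patients, 24 h excess | 5 × 24/164 = 0.73 | 98% | 26% |

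Two to five patients are 1.2% to 3.0% of an arm.

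**The case against.** The strongest reply is that the sentence on captured data is a retention rule: what has been collected is kept. It does not say that only those data are used, nor that follow-up stops. Study visits and data collection schedules assessments up to hospital discharge without exempting medically withdrawn patients, and Statistical analysis expects few or no losses. That much stands, so a reader who infers that follow-up necessarily ends goes beyond the text. What remains is that leaving the study ordinarily ends study assessments, and nothing says these patients are an exception.

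Other objections stand in part:

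- **Who decides.** The rule does not say which investigator withdraws the patient. The one responsible for care is unblinded, but each site has at least two investigators, and a blinded one collects postoperative variables. Knowledge of allocation is possible rather than certain, and blinded collection does not help if collection stops.
- **Safety oversight.** A reader might infer that harms are hidden from the DSMB. The document does not support this. Trial organization sends study-related SAEs to the DSMB within 7 days and unexpected unrelated events twice a year, and plans a safety analysis at 50% inclusion. That channel does not fill in the endpoints.
- **Few cases.** Because controllers can be switched off within the trial, medical withdrawal from the INTELLiVENT-ASV arm may be rare.
- **Size.** An excess of 24 h is 4.8 times the planning SD, and losses confined to one arm are an assumption. A Wilcoxon test, which the plan allows for non-normal data, would be less sensitive to a few extreme durations than a difference in means.
- **Fuller documents.** A full protocol and an analysis plan are announced. An analysis plan can settle how withdrawn patients are analysed, but it cannot recover outcomes that were not collected.

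**Conclusion.** The point holds as a conflict between stated rules. The analysis set and the intention-to-treat statement keep medically withdrawn patients in. The withdrawal and complete-case rules, followed as written, can truncate or drop their ventilation duration, stay and mortality, with no sensitivity analysis for those outcomes. The accurate claim is that these data can be lost, not that they will be.

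The document does not allow the number, arm balance or direction to be determined. The range of 0.15 to 0.73 h (20% to 98% of the margin) rests on assumed one-arm losses of 2 patients with 12 h excess to 5 patients with 24 h excess, on the planning SD of 5.0 h and on a comparison of means. Balanced loss of similar patients gives about zero. A reader might extend the concern to the primary endpoint, but that covers only the first 2 h of ventilation and is little exposed. The change is worth making because it is cheap and protects the endpoint that determined the sample size.

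**What to change.** Reconcile Study dropouts and missing data with the analysis set in Statistical analysis and the intention-to-treat statement in the Discussion:

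1. State that, after an investigator withdraws a patient for medical reasons, and unless the patient withdraws consent, collection continues to hospital discharge for ventilation duration, re-intubation, complications, ICU and hospital stay, and vital status.
2. State that these patients are analysed in the allocated group.
3. Report the number of such withdrawals and the reasons for them, per arm.

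This concerns data collection and analysis only. No rule is proposed on when the allocated mode is stopped or on any other clinical decision.

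The cost is a few sentences in the protocol and slight extra data entry for a few patients, since the same variables are already scheduled under Study visits and data collection.
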